### Report:

Patient inclusion/exclusions are enumerated. Baseline demographic and ASCVD Risk characteristics will be described by exposure group. [Table 1](#), [Figure 1](#)

## 7. Primary Endpoint

Electronic consenting on the Mytonomy website is recorded as Consent, Declined, or Not Consent. For the primary endpoints the endpoint will be dichotomized as yes (Consent) vs. no (Declined or Not Consent).

## 8. Secondary Endpoint

Patients who consent will answer 7 questions testing their comprehension of the consent form. The secondary endpoint will count the number of correctly answered questions (out of 7). For the main analysis

of the secondary endpoint, comprehension will be dichotomized as scores  $\geq 5$  (at least 5 questions correct) or scores  $<5$  (fewer than 5 questions correct).

Report:

Comprehension of consent quiz questions and responses by question number. [Table S1.1](#)

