#### 4.2.6 eConsent comprehension

Through the use of conversational verbiage and the ability to stop, start and rewind, our group believes the eConsent will result in greater participant comprehension of the study – thus, a more *informed* consent. In turn this may lead to a more engaged trial participant who is more likely to complete the study and not be lost to follow up. This has not been shown in a randomized manner and thus we will be evaluating comprehension across all four arms of the consent: three videos and one text-based.

Upon signing the form each participant will be asked a total of five questions. If the answer is incorrect the participant will be provided with the correct answer, but this will not prevent them from signing the

consent form. At the completion of this <2-minute quiz, participants will be able to electronically sign the form and have a PDF of the signed form emailed to their personal email address.

**Figure 2.** Consent pathway.

[figure not shown]

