## **2. Study Design**

### **2.1 Overview**

Invitations to participate in the study were sent to patients by email or MyChart message (See protocol section 2.2).

Upon delivery of message, participants will be given a link to access a study Mytonomy website. Once potential participants arrive at the study landing page hosted by Mytonomy, Inc. (through the eRecruitment process), they will see a brief description of the study along with an introductory video. Individuals will then be able to click on a 'Click to consent' link to begin the consent process. Consecutive individuals who click on the 'click to consent' on the 'landing' page will be randomized to consent via one of four consenting methods. Potential participants will be presented with the first page of the consent portal which will provide them IRB-approved consent form to review to sign and view one of the 4-types of consent-content mentioned above that they will be randomized to. Consenting on the study website is the primary outcome variable which will be dichotomized as consented (yes vs. no) within a 6-month period from time of invitation.

Upon signing the form each participant will be asked a total of seven comprehension questions. If the answer is incorrect the participant will be provided with the correct answer. The number of correctly answered survey questions is a secondary endpoint which will be dichotomized at several cut points.

The over-arching hypothesis is that, an informed consent form that includes both text and an animated video will lead to greater completion of the consent form and greater comprehension of the consent form compared with a text only, physician video, or patient video consent form.

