#### Statistical Tests:

A robust log linear Poisson model will be used for modeling score on the Mytonomy website quiz  $\geq 5$  vs. scores  $<5$  as a function of consenting method to find the relative risk/risk ratio (RR) of high comprehension score. The model will be fit using Generalized Estimating Equations (GEE) to provide a robust estimates of the covariance. The hypothesis of no difference between exposure groups will be tested using the global test p-value for consenting method (3 df Wald test). A p-value  $< 0.05$  will be considered nominally statistically significant evidence of at least one difference between groups. Pairwise comparisons between consenting methods will be made using relative risks (95% confidence intervals), with 'Text Only' as the reference category.

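### Testing the seven-item comprehension score only at the ≥5 cut keeps about two-fifths of the information on a common shift; add one labelled ordinal analysis

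*Combined protocol and SAP*

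**What the plan says.** SAP Section 8 defines the secondary endpoint as the number of correct answers out of seven, and for the main analysis "of the secondary endpoint, comprehension will be dichotomized as scores" of at least 5 or below 5. Section 10.2 tests that binary variable: "A robust log linear Poisson model will be used for modeling score on the Mytonomy website quiz", with a 3 df Wald test at nominal 0.05 and relative risks against text only. Section 10.3 repeats the same binary outcome in subgroups. Section 10.1 describes the full score by arm, but no planned test uses it.

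SAP Section 2.1 says that the number of correct answers "is a secondary endpoint which will be dichotomized at several cut points". No cut other than 5 is named or tested anywhere. The documents give no reason for choosing 5, and no power or effect size for this endpoint.

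Protocol Section 4.2.6 describes a shorter quiz: "Upon signing the form each participant will be asked a total of five questions". The SAP uses seven throughout, and Table S1.1 lists seven.

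**The concern.** Comprehension is half of Hypothesis 4a. A count with six observed values (2 to 7) is reduced to pass or fail at a point that most participants exceed. In Table 2b, 620 of 884 (70%) score 6 or 7, and the test cannot tell those two scores apart, nor either of them from a 5. If the consent formats move comprehension as a whole rather than only across the line at 5, the planned test has much less power than the same scores could give, and its estimates are less informative. The open reference to several cuts also leaves it unclear which further binary analyses were intended.

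**Working it through.** **Inputs** (Table 2b, scores 2, 3, 4, 5, 6, 7)

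| Arm | Counts | N |
|---|---|---|
| Physician video | 2, 3, 26, 34, 104, 69 | 238 |
| Patient video | 1, 6, 19, 32, 82, 63 | 203 |
| Animated video | 2, 8, 25, 45, 84, 58 | 222 |
| Text only | 1, 7, 20, 33, 95, 65 | 221 |
| All | 6, 24, 90, 144, 365, 255 | 884 |

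**1. Reproduce Table 5.** Animated against text at ≥5: (187/222)/(193/221) = 0.842/0.873 = 0.965. The variance of the log ratio is 1/187 − 1/222 + 1/193 − 1/221 = 0.00150, so the SE is 0.0387 and the 95% CI is 0.894 to 1.041. Table 5 prints 0.96 (0.89, 1.04). The robust Poisson fit to all four arms gives a 3 df p of 0.775; Table 5 prints 0.77.

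**2. Information retained.** Under proportional odds, information on a common log odds ratio is proportional to 1 − Σp³ for the full score and to 3pq for a single cut.

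- Full score: the proportions are 0.0068, 0.0271, 0.1018, 0.1629, 0.4129 and 0.2885; Σp³ = 0.0998; 1 − 0.0998 = 0.900.
- Cut ≥5: 3 × 0.8643 × 0.1357 = 0.352; ratio 0.352/0.900 = 0.391, a loss of 61%.
- Cut ≥6: 3 × 0.7014 × 0.2986 = 0.628; ratio 0.698.
- Cut at 7: 3 × 0.2885 × 0.7115 = 0.616; ratio 0.684.

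**3. Dependence on the model.** Squared ratios of standard errors, proportional odds over logistic at ≥5, fitted to the 884 scores: 0.37, 0.37 and 0.40 for the physician, patient and animated contrasts. A latent-normal model gives 0.405/0.876 = 0.46. Retained information is therefore about 37% to 46%, a loss of 54% to 63%.

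**4. Power.** The documents give no effect size, so the odds ratios are assumptions. For two arms of n = 221 (N = 442), V = n²N/[3(N + 1)²] × information term: 33.0 with 0.900 and 12.9 with 0.352. Power = Φ(ln OR × √V − 1.96). At an odds ratio of 1.5 the full score gives Φ(0.405 × 5.745 − 1.96) = Φ(0.37) = 64%, and the cut gives Φ(0.405 × 3.592 − 1.96) = Φ(−0.50) = 31%. A two-proportion calculation for the cut, 0.864 against 0.905, gives 27%.

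| Assumed common OR | Full score | Cut at ≥5 |
|---|---|---|
| 1.3 | 33% | 14–15% |
| 1.5 | 64% | 27–31% |
| 2.0 | 98% | 58–70% |

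**5. What the scores show by analysis**

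| Analysis | Animated v text (95% CI) | Global p |
|---|---|---|
| RR, ≥4 | 0.99 (0.95, 1.03) | 0.49 |
| RR, ≥5 | 0.96 (0.89, 1.04) | 0.77 |
| RR, ≥6 | 0.88 (0.78, 1.004) | 0.19 |
| RR, 7 | 0.89 (0.66, 1.20) | 0.73 |
| Proportional odds, OR | 0.76 (0.54, 1.07) | 0.28 |
| Kruskal-Wallis, H = 3.80 | – | 0.28 |

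On one scale, the animated odds ratio at ≥5 is exp(−0.255) = 0.78 with SE 0.274, so 95% CI 0.45 to 1.33. The ordinal estimate, exp(−0.273) = 0.76 with SE 0.174, gives 0.54 to 1.07: nearly the same estimate with a much narrower interval. The ordinal odds ratios are 1.00 (0.72, 1.39) for the physician video and 1.02 (0.72, 1.45) for the patient video.

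**6. Is a common shift plausible?** Animated odds ratios at cuts ≥4, ≥5, ≥6 and 7 are 0.80, 0.78, 0.68 and 0.85, which is compatible with one. For the physician arm only the sparse ≥4 cut departs (1.75, SE of the log odds ratio 0.58).

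**The case against.** The best defence is that a threshold is a legitimate estimand. If the question is whether participants reach adequate comprehension, the relative risk of scoring at least 5 answers it directly and matches the model for the primary endpoint; a difference between 6 and 7 is then not lost information but a different question. That stands as a reason to keep the ≥5 analysis. It does not justify having no test of the full score, because the hypothesis speaks of greater comprehension, not of reaching a threshold.

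The 86.4% is an observed result, not a planning input, and the tables were generated in December 2023 and January 2024. Replacing the stated main analysis now, because the data favour another method, would be post hoc. That also stands, and it sets the form of the fix.

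The power figures are for two arms, while the SAP's test is a 3 df global one, and they depend on direction: a shift of the same size towards lower scores (odds ratio 1/1.5) gives the cut about 34% rather than 27%. The figures illustrate; they are not design values.

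Three stronger readings are tempting, and the documents do not support them. A reader might infer that the null result is an artefact of the cut: no cut and no ordinal test reaches 0.05, every interval against text only includes 1, and the animated arm, which the hypothesis expects to do best, is numerically lowest in all of them. A reader might infer that the rest of the distribution is ignored: SAP Section 10.1, Table 2b and Figure 3 present it by arm, and only the testing is binary. A reader might set the cut against the protocol's five-question quiz and conclude that it demands a perfect score: the quiz actually given had seven items.

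**Conclusion.** The point holds as a loss of precision. For detecting a common shift in scores, the ≥5 cut keeps 0.39 of the information under proportional odds, and 37% to 46% across the models tried. The loss exceeds half in each of them, and cuts at 6 or 7 would have lost about 30% and 32%. The advantage of the full score rests on the shift being roughly similar across cut points, which the observed odds ratios do not contradict; if an effect were confined to the line at 5, the gain would shrink or vanish.

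The formal conclusion on comprehension does not change. The practical gain is that a reader of Table 5 sees three ratios near 1, whereas the full score puts the animated arm at an odds ratio of 0.76 with an interval reaching just past 1, a more informative statement about the format that the hypothesis favours. This is a secondary endpoint tested outside multiplicity control, with no power claim attached, so an added analysis is proportionate.

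**What to change.** Keep the ≥5 relative risk as the stated main analysis. In SAP Section 10.2 add one analysis of the full 0–7 score with arm as the factor: a proportional-odds model with odds ratios and 95% intervals against text only, or a Kruskal-Wallis test if only a test is wanted. Label it a post hoc sensitivity analysis, because the results are already known. In a plan not yet run, it should be the main analysis with the ≥5 relative risk beside it. In SAP Section 2.1, replace the reference to several cuts with this single ordinal analysis.

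The cost is one model on data already held and a few words of SAP text. The downside is that a common odds ratio is less direct than a risk ratio and assumes a similar shift at each cut; showing the cut-specific odds ratios beside it lets readers judge that. The addition does not deal with the fact that only participants who consented are scored.

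As a separate wording item, reconcile the five questions in protocol Section 4.2.6 with the seven in the SAP.

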## 9. Primary Endpoint Analyses

### 9.1 – Primary Endpoint: Descriptive Summaries

Endpoint Description: Electronically consenting on the Mytonomy website dichotomized as yes vs. no.

Additional Stratification Factors: None

Statistical Tests:

The total number of consented participants and the total number of participants who landed on the Mytonomy website will be reported for all intervention groups using a binomial distribution with a normal approximation (i.e., Wald confidence limits) the proportion and 95% CI for consenting on the Mytonomy website will be reported.

Report:

Risk group and exposure groups will be enumerated and the proportion and 95% CI for landing will be reported. For patients who consented, the time from landing to consent will be summarized with descriptive statistics. [Tables 2a](#), [Table 2b](#)

### 9.2 – Primary Endpoint: Inferential Analyses

Endpoint Description: Electronically consenting on the Mytonomy website dichotomized as yes vs. no.

Statistical Tests:

A robust log linear Poisson model will be used for modeling electronically consenting on the Mytonomy website vs. not as a function of consenting method to find the relative risk/risk ratio (RR) of consenting. The model will be fit using Generalized Estimating Equations (GEE) to provide a robust estimates of the covariance. The hypothesis of no difference between exposure groups will be tested using the global test p-value for consenting method (3 df Wald test). A p-value  $< 0.04$  will be considered statistically significant evidence of at least one difference between groups. Pairwise comparisons between consenting methods will be made using relative risks (96% confidence intervals), with 'Text Only' as the reference category.

Report:

The associations between the consenting methods will be characterized by each groups as RR, the corresponding 96% confidence interval, and global p-value. [Table 3](#)

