### **2.2. Secondary Aims & Hypotheses**

Aim 3: Optimal Recruitment Strategies. We aim to determine optimal strategies to recruit patients into the study remotely, i.e. without requiring a formal clinic visit or the direct involvement of the patient's clinician. Specifically, we want to understand whether an initial message through personal email vs. MyChart message leads to greater engagement, and whether the content of the message affects engagement. We will do this by randomizing potentially eligible patients in a 2x2 factorial fashion to personal email vs. MyChart message, and to different message content.

Hypothesis 3a: An introductory message delivered through MyChart will lead to greater engagement (as assessed by clicking on the study website page to get more information) than will a message delivered through personal email.

Hypothesis 3b: For patients with obesity, a message conveying altruism will lead to greater engagement than a message conveying personal benefit.

Hypothesis 3c: For patients without obesity, a message conveying altruism will lead to greater engagement than a message conveying scientific importance.

**Aim 4: Optimal Consenting Strategies.** We aim to determine optimal strategies to consent patients into the study remotely, i.e. without requiring a formal clinic visit or the direct involvement of the patient's clinician. Specifically, we want to understand which of the following formats leads to greater completion of the consent form and greater participant comprehension of the consent form: text only vs. text + physician video vs. text + patient video vs. text + animated video.

**Hypothesis 4a:** An informed consent form that includes both text and an animated video will lead to greater completion of the consent form and greater comprehension of the consent form compared with a text only, physician video, or patient video consent form.

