#### 3.4 Multiplicity Adjustments

Multiplicity will be controlled at  $\alpha=0.05$  for the statistical tests associated with the primary objective. A single interim analysis of the primary endpoint was conducted at  $\alpha=0.01$ , leaving the remaining  $\alpha=0.04$  for the final analysis. A global 3 df hypothesis test of any difference between the four consenting strategies will be tested at  $\alpha=0.04$ , and confidence intervals for effect estimates for the primary endpoint (relative risks) will be reported with nominal 96% confidence. Multiplicity will not be controlled between the primary and secondary endpoint analyses, and the secondary endpoint will be tested at  $\alpha=0.05$ , and effect estimates reported with nominal 95% confidence intervals. Subgroup analyses for the primary

endpoint will be considered exploratory, with interactions tested at nominal  $\alpha=0.05$ . All other estimates will be reported with nominal 95% confidence limits.

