| Text and Patient Video                                                                                                     | 0.91 ( 0.8, 1.04)  |         |
| Text and Animated Video                                                                                                    | 0.99 ( 0.88, 1.13) |         |
| Text Only                                                                                                                  | Ref                |         |
| *RR= Relative Risk
If p-value<0.04 then there is a statistically significant of at least one difference between groups. |                    |         |

Generated from /dcric/study/tdh\_resilience/tables/aim 4/update2/Table3\_UPDATE\_1.4.24.sas on 23JAN2024 at 14:19.

**Table 4. Robust log linear Poisson regression for the association of the exposure group, sub groups and the interaction (exposure group x subgroups) of consenting on the Mytonomy website.**

|                         | Text and Physician
Video vs. Text Only
RR (95% CI) | Text and Patient
Video vs. Text Only
RR (95% CI) | Text and Animated
Video vs. Text Only
RR (95% CI) | Global
Interaction p-
value |
|-------------------------|----------------------------------------------------------|--------------------------------------------------------|---------------------------------------------------------|-----------------------------------|
| Age (Years)      |                                                          |                                                        |                                                         | 0.49                              |
| ≥60                     | 1.02 ( 0.87, 1.18)                                       | 0.93 ( 0.79, 1.09)                                     | 0.97 ( 0.83, 1.14)                                      |                                   |
| <60                     | 1.16 ( 0.97, 1.38)                                       | 0.88 ( 0.72, 1.09)                                     | 1.02 ( 0.85, 1.24)                                      |                                   |
| Race             |                                                          |                                                        |                                                         | 0.3                               |

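### Hypothesis 4a sets animated video against three other formats, but the SAP plans only comparisons with Text Only, so two of the three hypothesised contrasts are neither planned nor reported

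*Combined protocol and SAP*

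**What the plan says.** Protocol section 2.2 gives Hypothesis 4a in these words: "An informed consent form that includes both text and an animated video will lead to greater completion of the consent form and greater comprehension". The comparators, repeated in SAP 2.1 where this is called the over-arching hypothesis, are set by the words "compared with a text only, physician video, or patient video consent form". There is thus one index format and three comparators, for two endpoints.

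The inferential plan for the primary endpoint (SAP 9.2) has two parts.

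- A global test: "The hypothesis of no difference between exposure groups will be tested using the global test p-value for consenting method (3 df Wald test"), judged at 0.04.
- Effect estimates: "Pairwise comparisons between consenting methods will be made using relative risks (96% confidence intervals), with 'Text Only' as the reference category". SAP 3.4 sets the level: "confidence intervals for effect estimates for the primary endpoint (relative risks) will be reported with nominal 96% confidence".

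SAP 10.2 repeats the structure for comprehension at 0.05: "Pairwise comparisons between consenting methods will be made using relative risks (95% confidence intervals), with 'Text Only' as the reference category".

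Tables 3 and 5 each carry three risk ratios, all against Text Only. The subgroup tables (4 and 6) have only columns against Text Only.

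**The concern.** The hypothesis determines which contrasts answer the question. For 4a they are animated v text, animated v physician and animated v patient. The SAP plans animated v text, physician v text and patient v text. Only one of the three hypothesised contrasts is on the planned list, and this is so for both endpoints.

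The global test does not fill the gap. It has no direction and singles out no arm, so it can be significant for reasons unrelated to animation. The SAP has no rule linking the global result, or any set of contrasts, to a conclusion about 4a. Had animated video beaten text, the plan would still have had no analysis of whether it also beat the other two videos.

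**Working it through.** **Inputs.** Consent counts are from Table 2a: physician 241/386, patient 203/383, animated 223/386, text 221/380. Counts scoring at least 5 on the quiz are from Table 5: physician 207/238, patient 177/203, animated 187/222, text 193/221. Table 5 labels all three video rows as physician video; Table 2b identifies the second and third as patient and animated.

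**Formula.** For arms with x₁/n₁ and x₂/n₂, log RR = ln[(x₁/n₁)/(x₂/n₂)] and SE = √(1/x₁ − 1/n₁ + 1/x₂ − 1/n₂). This is the robust Poisson variance for a model containing only arm; a GEE fit to the rebuilt data gave the same risk ratios against text, intervals and global tests. Limits are exp(log RR ± z·SE), with z = 2.054 for 96% and 1.960 for 95%.

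**Reproducing the plan's own figures.**

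| Contrast | Consent RR (96% CI), recomputed | Table 3 | Comprehension RR (95% CI), recomputed | Table 5 |
|---|---|---|---|---|
| Physician v text | 1.074 (0.952, 1.211) | 1.07 (0.95, 1.21) | 0.996 (0.928, 1.068) | 1 (0.93, 1.07) |
| Patient v text | 0.911 (0.798, 1.041) | 0.91 (0.8, 1.04) | 0.998 (0.928, 1.074) | 1 (0.93, 1.07) |
| Animated v text | 0.993 (0.875, 1.127) | 0.99 (0.88, 1.13) | 0.965 (0.894, 1.041) | 0.96 (0.89, 1.04) |

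The global Wald test for consent gives chi-square 6.97 on 3 df, p = 0.073 (Table 3: 0.07). For comprehension it gives 1.11, p = 0.775 (Table 5: 0.77). The tables reproduce, so further contrasts computed this way are on the same scale.

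**The two missing contrasts, consent.**

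- Animated v physician: ln(0.5777/0.6244) = −0.0776; SE = √(0.001894 + 0.001559) = 0.0588; RR 0.925 (0.820, 1.044), p = 0.19.
- Animated v patient: ln(0.5777/0.5300) = 0.0862; SE = √(0.001894 + 0.002315) = 0.0649; RR 1.090 (0.954, 1.245), p = 0.18.

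**The two missing contrasts, comprehension.**

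- Animated v physician: RR 0.968 (0.898, 1.044), p = 0.40.
- Animated v patient: RR 0.966 (0.894, 1.044), p = 0.38.

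**What the global consent test responds to.** Physician v patient alone gives log RR 0.1638, SE 0.0622, RR 1.178, nominal p = 0.0085. Its 1-df chi-square is (0.1638/0.0622)² ≈ 6.93, against 6.97 for the whole 3-df test. Animated v text contributes a 1-df chi-square of 0.01. Nearly all the signal is therefore a difference between two arms that 4a does not compare with each other and that Table 3 does not contrast.

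**The case against.** **Text is the natural reference.** Protocol 4.2 sets out to test video against text consent, 4.2.2 labels text as the standard of care, and Aim 4 is to find the best format. A text reference with a global test fits that aim. This stands, and it is why the reference should not be switched to animated video: doing so would drop two comparisons with standard of care. Treating every comparison with text as merely descriptive would also demote one of 4a's own three parts. But Protocol 4.2 also asks whether videos differ by who delivers the information, which supports adding contrasts between videos.

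**The phrase about pairwise comparisons might cover all six pairs.** Read alone it could. The same sentence fixes the reference, and every table shows only comparisons with text.

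**The plan can already answer 4a in the negative.** A reader might infer that it can neither confirm nor refute the hypothesis. That goes too far. If 4a requires animated video to beat all three formats, animated v text is a necessary part; it is planned, and it shows no superiority on either endpoint. What the plan lacks is a route to confirmation.

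**No information is lost.** A reader might infer that the two ratios cannot be known. They follow from the reported counts, as shown above; they are unplanned and unreported, not unobtainable.

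**The risk of misreading is hypothetical.** Table 3's footnote is modest: "If p-value<0.04 then there is a statistically significant of at least one difference between groups". It claims nothing about animation, and the observed p of 0.07 is not significant. This stands as to the results. The SAP still does not say that a significant global test would leave 4a undecided.

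**Conclusion.** The mismatch is real and affects both endpoints: two of the three contrasts that 4a names are missing from the plan and from Tables 3 and 5. The plan can fail to support 4a but cannot confirm it.

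No observed conclusion changes. The global consent p of 0.07 exceeds 0.04, and all four missing intervals include 1. The omission does hide one informative estimate: consent was lower with animated than with physician video (57.8% v 62.4%, RR 0.93), opposite in direction to the hypothesis, though compatible with no difference.

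A reader might infer that the study's conclusion about animated video is wrong or unsafe. The figures do not support that. This is a gap between question and analysis, to be classed as should-fix.

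The conclusion rests on two assumptions: that superiority to each of the three comparators is the intended meaning of 4a, which is the natural reading but is not stated as a decision rule; and that the tabulated counts are the analysis data, which the reproduction of Tables 3 and 5 supports.

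**What to change.** - **Add the contrasts.** Keep Text Only as the reference in SAP 9.2 and 10.2. Add animated v physician and animated v patient as linear contrasts from the same fitted models, at 96% confidence for consent and 95% for comprehension, and show them in Tables 3 and 5.
- **Label them post hoc.** The document is headed as statistical results and its tables are dated December 2023 to January 2024, so neither the contrasts nor the rule below can be presented as prespecified. Rewording 4a as video v text at this stage would be revising the hypothesis after seeing the results.
- **State the rule.** For each endpoint, 4a is supported only if animated video is superior to all three comparators. Because all three must succeed, no further alpha split among them is needed. If any single success were to count, a multiplicity rule would be required.
- **Limit the global test.** Say that a significant 3-df result alone does not support 4a.

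The cost is a few sentences and two more rows in each of two tables, with no new data. The all-must-win rule also has lower power than a single contrast. By simulation, assuming 384 per arm, 58% consenting in the other three arms, a true 10-point advantage for animated video and two-sided 0.04, power is about 60% for all three successes against about 80% for one contrast.
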